## Abstract

**Background:**

Preventing ischemia‒reperfusion injury (IRI) is a major issue in kidney transplantation, particularly for transplant recipients receiving a kidney from extended criteria donors (ECD). The main consequence of IRI is delayed graft function (DGF). Hypoxia is one of the key factors in IRI, suggesting that the use of an oxygen carrier as an additive to preservation solution may be useful. In the OxyOp trial, we showed that the organs preserved using the oxygen carrier HEMO2life® displayed significantly less DGF. In the OxyOp2 trial, we aim to definitively test and quantify the efficacy of HEMO2life® for organ preservation in a large population of kidney grafts.

**Methods:**

OxyOp2 is a prospective, multicenter, randomized, comparative, single-blinded, parallel-group study versus standard of care in renal transplantation. After the selection of a suitable donor according to the inclusion/exclusion criteria, both kidneys will be used in the study. Depending on the characteristics of the donor, both kidneys will be preserved either in static cold storage (standard donors) or on machine perfusion (for ECD and deceased-after-cardiac-death donors (DCD)). The kidneys resulting from one donor will be randomized: one to the standard-of-care arm (organ preserved in preservation solution routinely used according to the local practice) and the other to the active treatment arm (HEMO2life® on top of routinely used preservation solution). HEMO2life® will be used for ex vivo graft preservation at a dose of 1 g/l preservation solution. The primary outcome is the occurrence of DGF, defined as the need for renal replacement therapy during the first week after transplantation.

**Discussion:**

The use of HEMO2life® in preservation solutions is a novel approach allowing, for the first time, the delivery of oxygen to organs. Improving graft survival by limiting ischemic lesions is a major public-health goal in the field of organ transplantation.

**Trial registration:**

ClinicalTrials.gov, ID: NCT04181710. registered on November 29, 2019.

## Administrative information

Note: the numbers in curly brackets in this protocol refer to SPIRIT checklist item numbers. The order of the items has been modified to group similar items (see http://www.equator-network.org/reporting-guidelines/spirit-2013-statement-defining-standard-protocol-items-for-clinical-trials/).

## Introduction

### Background and rationale {6a}

Kidney transplantation is the treatment of choice for patients with end-stage renal disease, as it provides long-term benefits in terms of patient survival and quality of life [1]. However, this therapy is now a victim of its own success, with an increasing shortage of organs resulting in long waiting times and increased mortality on the waiting list. In 2019 in France, 3643 kidney transplants were performed for approximately 15 000 patients on the waiting list [2]. This has led to an expanded acceptance of donor organs: donors with risks identified as extended-criteria donors (ECD) or deceased-after-cardiac-death donors (DCD). These donors display a higher incidence of primary nonfunction (PNF) [3] and an increased rate of delayed graft function (DGF) [4]. If the causes of graft loss in the long term are multifactorial, involving factors related to the donor and secondary events in the recipient (infection viral, rejection, drug toxicity, hypertension, metabolic complications), acquired lesions secondary to ischemia‒reperfusion arise [5].

Ischemia–reperfusion is a complex pathophysiological process involving hypoxia and/or reoxygenation, ionic imbalance-induced edema and acidosis, oxidative stress, mitochondrial uncoupling, ATP depletion, coagulation and endothelium activation that is associated with a proinflammatory immune response (reviewed in [6]). I/R is also associated with the activation of Toll-like receptors responsible for the recruitment and activation of immune cells from both the innate and adaptive immune systems, the production of proinflammatory cytokines and chemokines and the activation of the complement pathway (reviewed in [7]). The main consequences of renal ischemia–reperfusion are kidney graft PNF and DGF. It also favors acute rejection [8] and the development of interstitial fibrosis [9], which both have an impact on long-term graft outcome [10]. As these adverse effects (AEs) are most severe in nonoptimal grafts (those obtained from ECD or DCD donors), new approaches are needed to improve the recovery and preservation of kidney grafts [11], particularly those from high-risk donors.

Preservation solutions are based on the principle of hypothermia, which is to maintain organs in a solution at 4 °C to reduce metabolism. A recent meta-analysis suggested that the three most popular solutions (UW, HTK and Celsior) bring comparable risks of DGF [12]. Preservation solutions attempt to reduce the damage associated with ischemia‒reperfusion, but none provide a solution to hypoxia or the reoxygenation responsible for damage, whose deleterious effect on graft survival in the long term is well established. For the last five years, hypothermic machine perfusion (HMP) preservation is increasingly being used as an alternative to static cold storage (SCS) for the preservation of grafts obtained from donors. HMP relies on the recirculation of cold preservation solution through the vasculature of the organ in either a continuous or pulsatile manner. Recent studies have shown that the use of machine perfusion improves the recovery of graft function compared with SCS (rate of DGF from 26.5% to 20.8%) and graft survival [13, 14]. Even if machine perfusion preservation might be beneficial in limiting interstitial fibrosis and tubular atrophy [15], this approach can still be improved by increasing the oxygen supply. However, high concentrations of oxygen may favor the production of oxygen free radicals and promote tissue damage [16]. Several approaches have been investigated to supply oxygen to the organ, such as the two-layer preservation method using perfluorocarbons [17–19], the gaseous oxygenation of preservation solution by retrograde persufflation (effectiveness not determined)[20] and, more recently, a portable device for oxygenated perfusion that has been developed and tested in a pig model of autotransplantation [21]. This study clearly showed a benefit of oxygen in terms of renal function recovery and fibrosis at the 3-month kidney biopsy. Along these lines, the COMPARE trial showed that active oxygenation during preservation using oxygenated hypothermic machine perfusion improves kidney function in humans [22].

The medical additive HEMO_2_life®, an oxygen carrier developed by the HEMARINA French Company, is a natural extracellular hemoglobin isolated from the marine lugworm *Arenicola marina*. This biopolymer of high molecular weight (~ 3,600 kDa) has a high oxygen binding capacity, carrying up to 156 oxygen molecules when saturated (compared to 4 for human adult hemoglobin). It releases oxygen according to a simple gradient and exhibits intrinsic superoxide dismutase-like activity, preventing both the generation of potentially harmful heme-protein-associated free radical species and the release of hemoglobin degradation products [23–25]. Prior to transplantation, the addition of HEMO_2_life® to preservation solutions prevents the progressive decline in the dissolved oxygen concentration available for the graft [26]. The efficacy of HEMO_2_life® has been demonstrated in preclinical studies. In a porcine model of autologous transplantation after 24 h of cold ischemia in several preservation solutions, HEMO_2_life® significantly improved the recovery of renal function. After 3 months, animals that received kidneys treated with HEMO_2_life® exhibited better renal function and less interstitial fibrosis, tubular atrophy and inflammation on kidney biopsy [26, 27]. This protein is not glycosylated; does not induce any immunogenic, allergenic, or mutagenic responses; and is degraded into polypeptide chains and heme [23].

In a previous proof-of-concept study (the OxyOp trial), we showed that HEMO_2_life® used as an additive to the preservation solution was safe for the kidney graft and the transplant recipients and that the organs preserved using HEMO_2_life® displayed significantly less DGF [27, 28]. In this OxyOp2 clinical trial, we aim to definitively test and quantify the efficacy of HEMO_2_life® for organ preservation in a large population of kidney grafts.

### Objectives {7}

The present research focuses on the efficacy of HEMO_2_life® added to preservation solution in kidney transplantation.

The primary objective is:

To quantify the efficacy of HEMO_2_life® used as an additive to standard organ preservation solution to prevent DGF following renal transplantation.

The secondary objective is as follows:

To assess and compare graft and patient survival in the two groups (standard of care versus HEMO_2_life®)To assess the efficacy of HEMO_2_life® on renal parameters compared with the standard of care.To assess efficacy in specific populations with different donor types and preservation method (standard donors, ECD, DCD, SCS, machine perfusion, different perfusion solutions).To evaluate the impact of HEMO_2_life® on the degree and progression of interstitial fibrosis before implantation and in 3-month biopsies.To assess the safety profile of HEMO_2_life® for the graft and the graft recipient.

### Trial design {8}

OxyOp2 is a prospective, multicenter, randomized, comparative, single-blinded, parallel-group, superiority study versus standard of care in renal transplantation. After the selection of a suitable donor according to the inclusion/exclusion criteria, both kidneys will be studied. Depending on the characteristics of the donor and following the French recommendations for organ preservation (Agence de la Biomédecine), both kidneys will be preserved either in cold storage or on machine perfusion (Fig. 1). Basically, grafts from standard donors are preserved in cold storage, whereas grafts from extended criteria donors are preserved on machine perfusion. Each kidney will be allocated to a patient following the French organ allocation rules independently of the protocol. In accordance with the rules for assigning kidney transplants in France, one kidney is allocated and transplanted locally (local kidney) in the transplant center where the kidney has been retrieved (local waiting list), whereas the contralateral kidney is allocated based on the national waiting list (national waiting list).

**Fig. 1 Fig1:**
[figure not shown]
Flowchart of the trial design. H2L: HEMO_2_life®. SOC: Standard of Care

## Methods: Participants, interventions and outcomes

### Study setting {9}

All French centers performing adult renal transplantation will participate in the study. They will be divided into two groups. Thirteen centers (first-line) will be involved in organ procurement, randomization, administration of the study molecule, transplantation of the allocated kidneys and follow-up of the patients, whereas the other 19 centers (second-line) will only transplant the allocated kidneys and follow up the patients. Any graft pair retrieved in the participating first-line centers is eligible for inclusion.

### Eligibility criteria {10}

#### Inclusion criteria

For kidney graft:

any pair of kidneys retrieved from an adult donor in one of the first-line participating centers.any pair of kidneys from a deceased donor after brain or cardiac death (DBD or DCD) who was not opposed of the use of its donation to help scientific research (checking of the French National Registry for Refusal of Organ Donation).

For kidney recipient:

male or female renal allograft recipient at least 18 years old.patient who signed an informed consent form.patient receiving one graft from an included pair of kidneys.

#### Exclusion criteria

For kidney graft:

graft from a living donor.graft dedicated to multiorgan transplantation or dual kidney transplantation.donor registered in the French National Registry for Refusal of Organ Donation

For patient:

age less than 18 years.refusal to participate in the study.

### Who will take informed consent? {26a}

#### Donor

By definition, it will be impossible to get informed consent from the donors. However, according to French law, the grafts will be included in the study after we check the French National Registry for Refusal of Organ Donation to see if the deceased subject was not opposed to the use of such donation to help scientific research.

#### Recipient

The ethics committee recommended sending a general letter of information about the study to all the patients on the waiting lists of the participating centers. Just before transplantation, the recipients of the graft will be again informed orally by the investigator from the transplant center, and if they accept, they will be asked to sign an informed consent form for the collection of clinical and biological data and conservation of biological samples. A record will be made of which grafts are randomized in the study but grafted to recipients who refuse to give their consent to participate in this research. This file will be fully anonymized and will be limited to collecting information about the grafts, donors, surgical information and incidents for grafts preserved with HEMO_2_life®.

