## Assignment of interventions: allocation

### Sequence generation {16a}

Randomized allocation will be achieved through "Ennov Clinical", a secure server with access to the e-CRF, by the retrieving investigational team. The randomization will be stratified according to the donor type (standard donor/ECD/DCD) and the destiny of the kidney (local kidney/contralateral kidney).

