### Implementation {16c}

The surgeon in charge of the organ procurement is responsible for the randomization and the administration of the medical device.

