### Procedure for unblinding if needed {17b}

The surgeon performing the renal transplantation is not blinded so unblinding will not be necessary.

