## Statistical methods

### Statistical methods for primary and secondary outcomes {20a}

Full Analysis Population:All complete and concordant (according to the type of conservation: cold storage or perfusion machine) randomized pairs fulfilling the inclusion criteria with no exclusion criterion.Preemptive grafts will be excludedRandomized pairs who do not receive HEMO_2_life® will be excluded, provided that HEMO_2_life® cancellation is not related to graft function.

Extended Full Analysis Population (exploratory):All randomized grafts fulfilling the inclusion criteria and no exclusion criterion will be included.Preemptive grafts will be excludedRandomized pairs who do not receive HEMO_2_life® will be excluded provided that HEMO_2_life® cancellation is not related to graft function.

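### Recipient consent is sought after the kidney has been randomised and treated, and both efficacy populations require it, so entry to the primary analysis can depend on the arm

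*Protocol article*

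**What the plan says.** All references are to the protocol article.

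- **Randomisation and treatment.** Under Sequence generation {16a}, allocation is obtained "by the retrieving investigational team". Implementation {16c} adds: "The surgeon in charge of the organ procurement is responsible for the randomization and the administration of the medical device".
- **Consent.** Under Who will take informed consent? {26a}, Recipient: "Just before transplantation, the recipients of the graft will be again informed orally by the investigator from the transplant center". Those who accept then sign. The same section plans a record of "which grafts are randomized in the study but grafted to recipients who refuse to give their consent", so refusal after randomisation is foreseen.
- **Eligibility {10}.** The recipient inclusion criteria contain "patient who signed an informed consent form". The exclusion criteria contain "refusal to participate in the study".
- **Analysis populations {20a}.** The Full Analysis Population takes complete, concordant randomised pairs that meet the inclusion criteria and no exclusion criterion. The exploratory Extended population is defined per graft: "All randomized grafts fulfilling the inclusion criteria and no exclusion criterion will be included".
- **Blinding {17a, 17b}.** The product colours the solution red, and only the recipient is kept unaware. "The surgeon performing the renal transplantation is not blinded so unblinding will not be necessary".
- **Data on refusers {26a, 18a, 18b}.** Follow-up of refusers is described for HEMO2life grafts only, and is limited to graft, donor and surgical information and adverse events. DGF is not listed.
- **Related rules.** The definition of nonevaluable inclusions under Recruitment {15} does not name refusal. Nor does the missing-data rule under {20c}.

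**The concern.** A condition of entry that is settled after allocation, by people who may know the allocation, opens the analysis to post-randomisation selection. Whether a high-risk recipient is approached, and how participation is explained, could differ between arms.

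Pairing does not protect against this. The two kidneys share a donor, but the two recipients are different people whose own DGF risk is not matched. McNemar's test compares whichever recipients remain and cannot correct for how they came to remain. Because a refusal removes the whole pair from the Full Analysis Population, arm sizes stay equal and the counts alone would show nothing.

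The secure server described under Concealment mechanism {16b} hides the sequence from the person who randomises. It does not hide the arm from those who later enrol the recipient. Both stated efficacy populations carry the consent condition, so neither can serve as a check on the other. The bias could favour either arm.

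**Working it through.** **Step 1: order of events.**
1. Retrieval: the procurement surgeon randomises and treats the kidney ({16a}, {16c}).
2. The kidney goes to a recipient under national rules, one locally and one through the national list (Trial design {8}). The local kidney is transplanted in the centre that retrieved it.
3. Shortly before surgery, the recipient is asked to sign ({26a}).
4. Signature decides entry to both efficacy populations ({10}, {20a}).

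Consent follows allocation, and entry follows consent. The safety population is not defined through the inclusion criteria, so the point concerns the efficacy sets only.

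**Step 2: the plan's own figure.** Inputs from Sample size {14}: DGF 28% against 15%, alpha 0.03, power 80%. The sidedness of this first test is not stated; two-sided reproduces the figure. With pooled variance and no continuity correction, p̄ = 0.215:

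n = [2.170 × √(2 × 0.215 × 0.785) + 0.842 × √(0.28 × 0.72 + 0.15 × 0.85)]² / 0.13² = 180 per group.

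Then 180 / 0.8 = 225 pairs, or 450 patients. Both stated figures are reproduced and are not in dispute.

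**Step 3: illustration with selection in one arm (assumed).** No true effect, 28% DGF in both arms. A fraction f of HEMO2life recipients, with DGF risk 56% (twice the average), is not enrolled. There is no such selection in control. The rate among enrolled HEMO2life recipients is (0.28 − 0.56f) / (1 − f).

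- f = 0.05: 0.252 / 0.95 = 26.5%, a spurious benefit of 1.5 points.
- f = 0.10: 0.224 / 0.90 = 24.9%, a spurious benefit of 3.1 points, about a quarter of the planned 13.

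With independent pair members, the discordant proportion is about 0.39 to 0.40. At 180 pairs the standard error is about √(0.39 / 180) = 0.047. The shifts are about 0.31 and 0.67 standard errors. Against a critical value of 2.17, the probability of a false favourable result rises from 1.5% to about 3.2% and 6.7%.

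**Step 4: a second assumed model.** HEMO2life-arm refusal is 5% in recipients who would not have DGF and r in those who would. Control refusal is unrelated to outcome. The apparent HEMO2life rate is 0.28(1 − r) / [0.28(1 − r) + 0.72 × 0.95].

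| r | Spurious difference (points) | Two-sided rejection probability |
|---|---|---|
| 5% | 0 | 3.0% |
| 10% | 1.1 | 3.4% |
| 15% | 2.2 | 4.8% |
| 20% | 3.3 | 7.5% |
| 30% | 5.7 | 17.8% |

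**Step 5: cases without bias.** If the Step 3 selection acted equally in both arms, both rates would fall to the same value and the difference would be zero. Refusal unrelated to arm and outcome removes 1 − (1 − q)² of pairs for a refusal rate q per recipient: 6% of pairs at q = 3%, and 19% at q = 10%.

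**The case against.** The strongest reply is that the mechanism needs several things the article does not state.

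- **The consent-taker.** A reader might infer that consent is taken by an unblinded transplant team. The documents do not support that. They name an investigator at the transplant centre, and separately say that the transplanting surgeon is unblinded. They do not say that these are the same person, or that the consent-taker knows the arm when asking. The stated timing would even allow consent on admission, before the container is seen. This stands. What remains is that no rule prevents the consent-taker from knowing.
- **Existing safeguards.** The person who accepts or refuses is blinded, and organ allocation is independent of the protocol. Both limit the mechanism. Neither governs whom staff approach or how they present the study.
- **Design constraint.** Kidneys are randomised at retrieval in 13 centres and may be transplanted in any of 32 (13 + 19), so consent after randomisation largely follows from the design. That is fair. It does not prevent keeping the consent-taker unaware of the arm.
- **Lost pairs.** A reader might count the pairs lost to refusal as lost power. Recruitment {15} continues enrolment until 180 evaluable pairs are reached, so by plan the cost is recruitment effort.
- **The numbers.** The illustration puts all the selection in one arm and assumes independent pair members. If selection follows donor risk, dropping the whole pair removes that donor from both arms and reduces the bias. The figures show only what would follow from such selection.
- **Reporting detail.** Tables of refusals are usually left to the analysis plan, which is not shown. The two population definitions, however, are fixed in the article, and both carry the consent condition.

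**Conclusion.** The structural point holds. Consent follows randomisation and treatment, both efficacy populations depend on it, and no stated safeguard keeps the consent-taker unaware of the arm. Entry to the primary analysis can therefore depend on allocation.

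Whether it did, and by how much, cannot be judged from the document, because no refusal rate is given, overall or by arm. The 1.5 to 3.1 points and the rise in false-favourable probability to about 3% to 7% rest on the assumptions in Step 3: no true effect, selection in the HEMO2life arm only, doubled risk in those not enrolled, independent pair members, 180 pairs and a two-sided 0.03 level.

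Trial status reports 520 patients included and 160 pairs for analysis. A reader might take that attrition as evidence of refusals. The document does not break it down, and preemptive grafts, discordant pairs and nontransplanted kidneys are other stated reasons for exclusion.

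This should be addressed, but it is not evidence that the result is biased.

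**What to change.** **Design.** Specify that consent is taken on admission, before the container or machine is seen, by an existing team member who took no part in the retrieval and has not been told the arm. Record the time of consent. This reorders existing steps. Collecting signed consent across the whole waiting list would be a much larger undertaking and is not needed.

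**This trial.** The last patient was included in July 2022, so the change of order can serve only later trials. Two steps remain possible:
1. Report non-consent by arm and by local or contralateral kidney, from the planned record of randomised grafts whose recipients refused.
2. Add a sensitivity analysis of the primary outcome over all randomised, transplanted, non-preemptive grafts, with bounds for unconsented recipients in both arms. One bound sets DGF present for those in the HEMO2life arm and absent for those in control; the other reverses this. Bounds are needed because DGF is not among the data listed for refusers, and no follow-up of control-arm refusers is described.

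**Cost.** A little extra analysis and no new patients or visits. The bounds may make the result look less certain.
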